#### Outcome measures

##### Outcome 1: Smoking abstinence

In the CPRD smoking status is indicated by whether the patient is a current, former or never smoker. As GPs are paid to record smoking status smoking behaviour is robustly recorded in the CPRD.^21^ Marston *et al*^21^ found that 84% of patients had smoking status recorded within a year of registering at a GP, and that smoking prevalence rates by age were similar in CPRD and the Health Survey of England. Booth *et al*^22^ found that the difference in prevalence of smoking estimate between the CPRD and the Health Survey for England was less than 1%, and the mean difference was 0.1% (95% CI −1.5% to 1.7%). Using unpublished data from CPRD sampled as part of the research reported in Thomas *et al*^13^ we found that 74% of patients prescribed smoking cessation medication had a subsequent record indicating smoking status. Of these 66% were indicated as current smokers and 33% as ex-smokers. We will initially define a patient as relapsed if they have any record indicating that the patient is a current smoker after their first prescription of a smoking cessation therapy. We will not be able to determine the smoking status of patients who do not return to the GP. Therefore, we will perform sensitivity analyses to examine whether the assumptions made about the smoking status of individuals who are not observed affect the results. For example, we will conduct a sensitivity analysis to see if the results are altered by assuming that patients with missing data have relapsed, or by assuming that patients with missing outcome data have achieved abstinence.

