#### Analysis 1: Conventional cox regression

In our first analysis, a conventional observational analysis, we will estimate HRs of the outcomes using Cox-proportional hazards models and the actual prescriptions issued to the patients.^29^ Each patient's date of entry into the cohort will be the date they were first prescribed a smoking cessation therapy. The date of exit for each outcome will be the date on which they first have an event, or are censored due to end of follow-up or death or leaving the practice. We will report these associations adjusted for basic confounders (age and gender), and results adjusted for all measured covariates described above.

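### The two named scenarios for patients with no later smoking record treat both drugs alike, so they test unequal non-return but not relapse among the unrecorded that differs by drug

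*Protocol article*

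**What the plan says.** All of the following is in the protocol article.

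- **Extent of missing status** (Outcome 1: Smoking abstinence). From the investigators' own earlier data, "74% of patients prescribed smoking cessation medication had a subsequent record indicating smoking status". The split among patients with such a record is then given: "Of these 66% were indicated as current smokers and 33% as ex-smokers". Both figures pool the two drugs.
- **Definition of relapse** (same section). A patient has relapsed on "any record indicating that the patient is a current smoker after their first prescription of a smoking cessation therapy".
- **Stated limitation** (same section). "We will not be able to determine the smoking status of patients who do not return to the GP".
- **Planned response** (same section). "we will perform sensitivity analyses to examine whether the assumptions made about the smoking status of individuals who are not observed affect the results". The text continues "For example, we will conduct a sensitivity analysis to see if the results are altered" and names the two scenarios: by "assuming that patients with missing data have relapsed, or by assuming that patients with missing outcome data have achieved abstinence". Neither distinguishes varenicline from NRT.
- **Deaths and leavers** (Analysis 1: Conventional cox regression). Patients exit at their first event or "are censored due to end of follow-up or death or leaving the practice".
- **Effect scales.** The Cox and propensity-score analyses report hazard ratios. The instrumental variable analysis reports risk differences.

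**The concern.** Smoking abstinence is the first study aim, and 26% of patients are expected to have no later record. If that share carries over to the expected 180 000 patients, it is about 46 800 people (0.26 × 180 000). The comparison is not randomised, so patients who do not come back after varenicline may differ in relapse from those who do not come back after NRT.

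A scenario that assigns one value to every unrecorded patient holds that difference at zero. Moving the common value from all relapsed to all abstinent changes the level of relapse on both drugs but need not change the contrast. Two similar results could then be read as showing that non-return does not matter, when the assumption most able to change the answer was never varied.

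**Working it through.** The plan gives no contrast by drug and no sensitivity result for this outcome, so there is no figure of its own to reproduce. The check is algebra, then an illustration.

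**Notation.** V is varenicline and N is NRT; m is the share with no later record, r is relapse among the recorded, and u is relapse among the unrecorded. RD is relapse on V minus relapse on N.

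**Identity.**

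- True RD = A + mV·uV − mN·uN, where A = (1−mV)·rV − (1−mN)·rN.
- All unrecorded abstinent (u = 0): RD = A.
- All unrecorded relapsed (u = 1): RD = A + (mV − mN).

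The scenarios differ by exactly mV − mN. They are guaranteed to bracket the truth when uV = uN, because RD then equals A + u·(mV − mN). Without that condition RD can lie anywhere from A − mN to A + mV, a width of mV + mN. With 26% missing on each drug, the scenarios span 0 points of a possible 52. With an assumed 22% v 30%, they span 8 of 52.

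**Inputs for the illustration.** The pooled 26% missing (100% − 74%) is from Outcome 1. The drug-specific rates are assumptions: recorded relapse 60% on V and 70% on N, and 26% missing on each. These match the pooled 66% if 40% of recorded patients took varenicline (0.4 × 60 + 0.6 × 70 = 66).

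| Assumption for the unrecorded | V | N | RD (points) |
|---|---|---|---|
| All abstinent | 0.74×0.60 = 44.4% | 0.74×0.70 = 51.8% | −7.4 |
| All relapsed | 44.4 + 26 = 70.4% | 51.8 + 26 = 77.8% | −7.4 |
| 80% relapse on V, 60% on N | 44.4 + 20.8 = 65.2% | 51.8 + 15.6 = 67.4% | −2.2 |
| V all relapsed, N all abstinent | 70.4% | 51.8% | +18.6 |
| V all abstinent, N all relapsed | 44.4% | 77.8% | −33.4 |

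The tipping-point gap uV − uN is 0.074/0.26 = 0.285, so about 28 points.

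**Other scales.** The relapse risk ratio moves a little between the two named scenarios: 44.4/51.8 = 0.86 and 70.4/77.8 = 0.90. A hazard ratio approximated as ln(abstinent share V)/ln(abstinent share N) barely moves: ln 0.556/ln 0.482 = 0.80 and ln 0.296/ln 0.222 = 0.81.

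**A smaller recorded effect.** With recorded relapse of 64% v 70%, both scenarios give 0.74 × (−6) = −4.4 points. The tipping gap falls to 0.0444/0.26, about 17 points.

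**Unequal missing shares** (recorded relapse again 60% v 70%).

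| Missing V v N | All abstinent | All relapsed |
|---|---|---|
| 22% v 30% | 46.8 − 49.0 = −2.2 | 68.8 − 79.0 = −10.2 |
| 20% v 32% | 48.0 − 47.6 = +0.4 | 68.0 − 79.6 = −11.6 |

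Here the named pair does separate, and in the second row it changes sign.

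**The case against.** Several objections have force.

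- **The list is open.** The scenarios are introduced as examples, and a condensed article may leave further ones to the full protocol. This stands: the plan does not rule out drug-specific scenarios. But these two are the only ones named and the text commits to them, so their limit is worth stating.
- **The named pair is not uninformative.** A reader might infer that the scenarios return the same contrast whatever the truth and cannot test non-return at all. The document does not support that. It gives only a pooled 74%, equal shares cannot be presumed in a non-randomised comparison, and the second table shows that the pair can reveal instability from unequal non-return.
- **Deaths and leavers.** A reader might also infer that the all-relapsed scenario turns deaths and leavers into relapses, mainly on NRT, given the adjusted mortality hazard ratio of 0.49 under Power calculations. Outcome 1 does not say that they count as missing, and Analysis 1 censors them. The hazard ratio comes without a baseline rate. The one absolute contrast given there, 0.7 per 1000 at 9 months (95% CI −3.3 to 4.7), is under half a percentage point at either limit. The argument also presupposes unequal missingness, so it cannot be combined with the equal-share illustration.
- **The rates are assumed.** True. Nothing in the document says that unrecorded patients on varenicline relapse more. The illustration shows what the scenarios cannot detect, not what is likely.
- **Prior GP visit frequency is a covariate.** Adjusting for it may reduce differences in who returns. It does not show that unrecorded patients with similar covariates relapse equally on both drugs.

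**Conclusion.** The point holds as a cheap improvement, not as an error in the plan. The two named scenarios vary the missing outcome equally on both drugs. On the risk-difference scale they differ only by the gap in missing share, and they leave untested any drug difference in relapse among the unrecorded. That follows from the algebra and needs no assumed rates.

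The sizes do rest on assumptions. With 60% v 70% recorded relapse and 26% missing on each drug, both scenarios give −7.4 points, the possible range is −33.4 to +18.6, and the sign changes at a gap of about 28 points. How far the two scenarios would separate in the real data depends on missing shares by drug, which the article does not report.

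A lesser point is that relapse requires a current-smoker record, so a patient with no record may already count as not relapsed in the main analysis. On that reading the all-abstinent scenario adds little to it.

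**What to change.** Keep both scenarios and add three things:

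1. Report the share with no later smoking record separately for varenicline and NRT.
2. Vary relapse among the unrecorded separately by drug over a grid. Report the gap between drugs at which the conclusion changes, and judge whether a gap of that size is plausible.
3. Report the two opposite-extreme bounds (all relapsed on one drug, all abstinent on the other, and the reverse).

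Apply the scenarios to patients still alive and registered, with deaths and leavers censored as in Analysis 1, and say so in Outcome 1.

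The cost is a few re-runs on the same data. The reported range will be wider and less favourable than the two named scenarios alone would give.

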##### Outcome 2: Frequency of GP and hospital attendance

We will define service use as the number of visits to GP and hospitals in the 3, 6, 9, 12, 24 and 48 months after first prescription. We will define GP appointments using the clinical data file of the CPRD. This includes all the diagnoses and symptoms that GPs record about all of their patients. As with the other outcomes, the vast majority of diagnoses and symptoms include the date on which the data were added to the database. We will use these dates to calculate the number of times each patient attends primary care. We will define the hospital visits outcome using the linked HES data. We will investigate all-cause hospitalisation and three specific causes of hospitalisation: (1) diseases of respiratory system (ICD-10=J00-J99), (2) cardiovascular disease (ICD-10=I00-I52) and (3) anxiety and depression (ICD-10=F31.3, F31.4, F31.5, F32, F40-F48). Causes of hospitalisation are available for approximately half of the sample. Again these data contain the date on which the event occurred, which we will use to define attendance to secondary care within 3, 6, 9, 12, 24 and 48 months after first prescription.

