## Abstract

**Introduction:**

Smoking is a major avoidable cause of ill-health and premature death. Treatments that help patients successfully quit smoking have an important effect on health and life expectancy. Varenicline is a medication that can help smokers successfully quit smoking. However, there are concerns that it may cause adverse effects, such as increase in the occurrence of depression, self-harm and suicide and cardiovascular disease. In this study we aim to examine the effects of varenicline versus other smoking cessation pharmacotherapies on smoking cessation, health service use, all-cause and cause-specific mortality and physical and mental health conditions.

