## Introduction

Smoking is the major cause of preventable morbidity and mortality in the UK and internationally.^1^
^2^ Smoking is also the principal cause of health inequalities and is responsible for most of the difference in healthy life-expectancy between the richest and poorest in our society^3^ and those with and without mental health problems.^4^
^5^ Smoking-related illnesses are estimated to cost the NHS approximately £5billion per year.^6^ Varenicline has been shown to be the most clinically effective smoking cessation medicine for short-term abstinence in randomised controlled trials (RCTs).^7^ However, there is relatively little evidence for its long-term effectiveness and impact on clinical outcomes.

Concerns have been raised that varenicline may be associated with a higher risk of adverse events, including suicide and self-harm and cardiovascular events, than other smoking cessation interventions.^8–11^ In 2009, the US Food and Drug Administration (FDA) mandated that varenicline carry a black box warning (the agency's strongest safety warning) highlighting the increased risk of suicidal ideation and depression in patients prescribed varenicline. This was based on spontaneous reports to the FDA Adverse Events Reporting (FDA AERS) database.^12^ These warnings are meant to indicate causal effects of pharmaceuticals. However, there are an increasing number of experimental and observational studies that suggest there is little difference in risk of adverse neuropsychiatric effects of varenicline compared to nicotine replacement products.^11^
^13^ In October 2014, the FDA decided that the black box warning on varenicline should remain; it is expected that this guidance will be updated after publication of the results of the EAGLES randomised trial in late 2015.^14^
^15^

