### Study aims

What is the effect of varenicline on smoking abstinence? We will investigate the effects of varenicline on smoking abstinence because existing evidence from RCTs typically only followed participants for 1 year, and are not informative about long-term outcomes.What are the effects of varenicline on NHS service use? We will investigate the effects of varenicline prescriptions on all-cause primary and secondary care utilisation because smoking increases morbidity and imposes major costs on the healthcare services.^16^What are the effects of varenicline on all-cause and cause-specific mortality? We will investigate the incidence illnesses in the Clinical Practice Research Database (CPRD) using primary care diagnoses, admission to secondary care using ICD-10 codes, and Office of National Statistics (ONS) mortality records to maximise the number of events detected.What are the effects of varenicline on common physical and mental health conditions? We will investigate the effects of varenicline on rates of cardiovascular outcomes and respiratory illnesses, as previous research has suggested that patients prescribed varenicline may have different rates of these outcomes.^9^
^10^ Second, we will investigate the effects of varenicline on rates of depression and anxiety because there has been some reports that varenicline may reduce the risk of these outcomes.^13^We will also examine differences in smoking cessation medication effectiveness by socioeconomic position. A recent systematic review reported that stop-smoking services may be helping to reduce inequalities in smoking prevalence by preferentially targeting smokers of lower socioeconomic position (SEP). Data from primary care records The Health Improvement Network (THIN) show that between 2008 and 2010, smokers in more deprived groups were more likely to receive smoking cessation interventions.^17^

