##### Outcome 3: All-cause and cause-specific mortality

We will define all-cause and cause-specific mortality using the linked ONS mortality data set. These include the date of death and cause of death using ICD-9 codes. We will investigate three specific causes of mortality: (1) diseases of respiratory system (ICD-10=J00-J99), (2) cardiovascular disease (ICD-10=I00-I52), and (3) anxiety and depression (ICD-10=F31.3, F31.4, F31.5, F32, F40-F48). We will use validated code lists for each outcome.

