##### Outcome 4: Incident respiratory illness, myocardial infarction, depression or anxiety

We will define the adverse event outcomes using the diagnosis records from the Clinical and Referral files in the CPRD. These files record all the diagnoses that the GPs input into their computer system. Each record in the table is given a diagnosis code based on the Read code categorisation. We will use validated Read code lists, for the three adverse event outcomes, respiratory illnesses, myocardial infarction or depression and anxiety, please see the cited papers for Read code lists.^23–25^ For eligible patients we will extract all records from the Clinical and Referral Tables that indicate the patient either received a specific diagnosis or were referred for a specific diagnosis. As with the therapy records for prescriptions described above, each Clinical and Referral Record indicates the date the information was inputted into the system. We will use this date to define the date that the diagnosis was performed. We will define a set of outcomes within 3, 6, 9, 12, 24 and 48 months after first prescription.

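### The outcomes labelled cardiovascular disease cover ICD-10 I00-I52 only, and the GP-recorded outcome is myocardial infarction only, so no cause-specific outcome is defined to identify cerebrovascular or peripheral arterial events

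*Protocol article*

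**What the plan says.** The concern and the aim are worded broadly. The Abstract gives the possible harm as "increase in the occurrence of depression, self-harm and suicide and cardiovascular disease". The Introduction refers to a "higher risk of adverse events, including suicide and self-harm and cardiovascular events". Under Study aims the article says "We will investigate the effects of varenicline on rates of cardiovascular outcomes and respiratory illnesses". The Methods paragraph of the Abstract lists death from cardiovascular disease among the outcomes.

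The definitions are narrower:

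- **Outcome 2 (hospital attendance).** "We will investigate all-cause hospitalisation and three specific causes of hospitalisation"; the second and third of these are given as "2) cardiovascular disease (ICD-10=I00-I52) and (3) anxiety and depression".
- **Outcome 3 (mortality).** The same range is used for deaths: "2) cardiovascular disease (ICD-10=I00-I52), and (3) anxiety and depression".
- **Outcome 4 (GP diagnoses).** Code lists are cited "for the three adverse event outcomes, respiratory illnesses, myocardial infarction or depression and anxiety".

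The respiratory outcome beside the cardiovascular one in Outcomes 2 and 3 takes J00-J99. The article mentions neither stroke nor peripheral arterial disease, whether to include or to exclude them, and gives no reason for ending the cardiovascular range at I52.

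**The concern.** Cardiovascular disease in its ordinary sense includes cerebrovascular and peripheral arterial disease. The range I00-I52 stops before both, and the GP-recorded outcome narrows the field further, to one cardiac event. The label and aim therefore promise more than the codes measure.

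What is at stake is the reach of the safety conclusion. The section on ethics and dissemination says that recommendations based on the findings will be sent to the FDA and the MHRA. A result labelled cardiovascular disease, null or otherwise, would rest on I00-I52 and myocardial infarction, while a reader going by the label could take it to speak to stroke and arterial disease as well.

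**Working it through.** The plan has no figure of its own to reproduce here. The check compares code ranges and then follows an excluded event through the planned analyses.

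**Inputs.** Admission and death range: I00-I52 (Outcomes 2 and 3). GP outcome: myocardial infarction (Outcome 4). The contents of the ICD-10 blocks come from the standard classification that the article uses, not from the article itself.

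**Step 1: is each block inside I00-I52?** Three-character codes falling in the range:

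| Block | Content | Codes inside I00-I52 |
|---|---|---|
| I20-I25 | ischaemic heart disease | 6 of 6 |
| I60-I69 | cerebrovascular disease | 0 of 10 |
| I70-I79 | diseases of arteries | 0 of 10 |

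The range is not a narrow ischaemic set either. It also takes in rheumatic, hypertensive, pulmonary and other heart disease, so a focus on ischaemic events does not explain where it ends.

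**Step 2: does any other cause-specific outcome take up the missing blocks?** The other specific causes in Outcomes 2 and 3 are respiratory disease and anxiety or depression. Those in Outcome 4 are respiratory illness, myocardial infarction, and depression or anxiety. None is defined on cerebrovascular or arterial disease.

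**Step 3: where do these events go?** An admission coded only in I60-I79 counts in all-cause hospitalisation, and a death coded only there counts in all-cause mortality. In the Cox models (Analyses 1 and 2), exit is at the first event, death, leaving the practice or end of follow-up. A death from stroke is then a censoring in the cardiovascular mortality model. A stroke admission leaves the patient at risk, without an event, in the cardiovascular admission model. In the instrumental variable analysis (Analysis 3), outcomes are classed by fixed windows from 3 to 48 months, and neither would be a cardiovascular event in any window.

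**Step 4: how many events are affected?** This cannot be computed. The article gives no cerebrovascular or arterial rates. Its Power calculations section reports 3144 cardiovascular admissions among 1022 patients within 2 years, but states no code range, so that count cannot be split into events inside and outside I00-I52.

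**The case against.** The strongest case for the plan is that it is open about its definition. The range is printed beside the label in both places, and Outcome 4 says myocardial infarction and claims nothing broader. A mainly cardiac composite can be a legitimate choice, and nothing requires every outcome to use a whole ICD chapter because the respiratory one does. The aim refers to earlier research that is not at hand, and that research may have concerned cardiac events only. All of this stands as a reason why I00-I52 might be kept. It does not remove the mismatch, because the article neither says that the restriction is deliberate nor narrows its aim to fit.

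Several stronger readings are tempting, but the document does not support them:

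- **That stroke and arterial events are never counted, or that any signal in them is wholly missed.** They enter all-cause admission and all-cause mortality. The signal there is diluted and cannot be attributed to a cause, but it is not absent.
- **That a patient with a stroke is event-free for every cardiovascular outcome.** The article does not say whether only the primary diagnosis or underlying cause counts, or any coded position. If any position counts, a stroke admission that also carries a hypertension code would qualify through I00-I52. The same patient may also have a separate I00-I52 event.
- **That the plan itself names stroke as a risk.** It names cardiovascular disease, events and outcomes; stroke is included only through the ordinary meaning of those words.
- **That the loss of precision can be quantified.** Any inflation of the standard error needs the share of circulatory events outside I00-I52, which is not given. A formula for the log hazard ratio would also not carry over to the risk differences of Analysis 3: adding events to an uncommon binary outcome raises its variance. The plan judges its event numbers sufficient, and no shortfall is shown.

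A promise under Outcome 3 to use validated code lists might suggest that the final list could be wider. It does not override the explicit range printed in the same paragraph.

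**Conclusion.** The point holds as a mismatch between what the study says it examines and what its cause-specific outcomes are defined to capture. Admissions and deaths labelled cardiovascular disease mean I00-I52, and the GP outcome is myocardial infarction. A difference between varenicline and nicotine replacement therapy in cerebrovascular or peripheral arterial events would not be identified in any result carrying the cardiovascular label.

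The size in events or precision cannot be given from the document. The conclusion rests on the standard content of the ICD-10 blocks I60-I69 and I70-I79, on the ordinary meaning of cardiovascular, and on the ranges being applied as printed. Step 3 of the check further assumes that the event carries no additional code inside I00-I52. The point is worth settling before analysis because it determines what the study can say on cardiovascular safety. It does not show that the I00-I52 result would itself be biased.

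**What to change.** For Outcomes 2 and 3, define cardiovascular disease as I00-I79 and report three components beside it: I00-I52, I60-I69 and I70-I79. The planned I00-I52 result is then kept in full and the missing events become visible under their own cause. The hospital and mortality records are already being linked, so the change is a wider code range and some extra rows in the results. The small downside is a more mixed composite, in which an effect confined to one component could be diluted; reporting the components deals with that.

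If the authors prefer to keep the range, they should state I00-I52 wherever the outcome is reported, including the abstract of the results paper. They should also say that the safety conclusion does not extend to cerebrovascular or peripheral arterial disease. That costs a few sentences. Renaming the outcome heart disease would not be accurate, since the range also contains hypertensive and pulmonary circulatory disease. Neither the whole chapter I00-I99 nor a new GP-recorded stroke outcome is needed to resolve the point.
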